### Fear of Falling Sub-Study

#### Procedures

In this longitudinal study, FLASSH participants from both the intervention and the control groups recruited from the sites in Melbourne, Australia will be included. This is estimated to be approximately half the overall project sample. Participants will be assessed at baseline, at four monthly intervals, and following any fall throughout the 12 month study period by a researcher blind to group allocation. Assessments will be conducted in the participant's home, and at each time-point, the following will be assessed:

(i) fear of falling (FES-S) [39,40]

(ii) gait and balance (5mwt [33], TUG (single and dual tasks) [34,35], Step Test [29])

(iii) activity (HAP-AAS [36]).

#### The study outcomes

The primary outcomes for this study will be fear of falling (FES-S), gait (gait velocity, TUG-single and dual), balance (ST), and activity level (HAP-AAS).

#### Sample size

It is estimated that approximately half of the overall sample will be included in this sub-study, giving a sample size of 80. The sample will include participants from the control and intervention arms of the main study.

#### Statistical methods

Descriptive statistics and multivariate analysis of variance will be used to determine changes in fear of falling and physical function between control and intervention groups, and faller and non-faller groups over time. Time series analyses and individual case analysis will be used to identify links between fall events and changes in fear of falling.

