At present there are no published randomised controlled trials investigating the effectiveness of falls prevention strategies in stroke survivors. There is, however, evidence for the effectiveness of single and multi-factorial interventions in older community-dwelling people [15]. Exercise, including components of strength and balance, but not necessarily including a walking program, appears to be effective in preventing falls in older adults [16,17], and other interventions such as home modification and reduction in psychotropic medication have also been shown to be effective [18,19]. While it is likely that some of the approaches shown to be effective in reducing falls in older people generally may also be effective in people with stroke, there are additional stroke-specific risk factors, for example inattention or neglect, which might influence uptake and effectiveness of interventions in the stroke population. The purpose of this randomised controlled trial is to determine whether an individualised, multi-factorial intervention is effective in reducing falls in people with stroke following discharge from rehabilitation.

Fear of falling is a key factor in relation to falls [20]. Even in the absence of physical injury, a fall can have negative functional and psychological consequences, including loss of confidence or fear of falling, which can lead to activity restriction. Restricting activity may lead to further loss of strength or heightened balance impairment, which then predisposes an individual to further falls.

It has been shown that fear of falling is common in older adults [21] and although there are few published studies about the prevalence in the stroke population, it appears to be present in stroke survivors [22,23]. There is evidence to support an association between falls, fear of falling and function in older people [24] and in stroke survivors [25]. However, it is not clear whether there is a causal relationship, that is, whether a fall causes fear of falling, whether fear of falling precipitates a fall, or whether a third factor causes both. While there are several cross-sectional studies which highlight the association between falls, fear of falling and function [22,25], longitudinal studies are required to evaluate changes in fear of falling and function over time, particularly in relation to the short-term effects of a fall.

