If a reduction in falls is observed, it is important to understand the mechanisms by which this has occurred. The reduction in falls may be secondary to an improvement in stability, or it may reflect increased caution when performing activities such as walking. The impact of the intervention on stability during walking is particularly pertinent, as the control of balance while walking is complex due to the inherent instability and dynamic nature of the task [26]. Examination of stability during walking will provide insight into the mechanisms by which the intervention may have an effect on reducing falls. Obstacle crossing has been shown to be a useful paradigm for exploring stability in walking following stroke [27,28].

The aims of this study are therefore threefold:

(i) to evaluate the effectiveness of a multi-factorial falls prevention program for stroke survivors returning home after rehabilitation,

(ii) to examine the temporal relationship between fear of falling, falls and function in the above population, and

(iii) to evaluate the contribution of gait impairments to the task of obstacle crossing in the context of a falls prevention program.

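### The faller/non-faller MANOVA in the fear-of-falling sub-study is poorly suited to its temporal aim, and no event-timed analysis is named for function or for fear preceding falls

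*Protocol article*

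**What the plan says.** Aim (ii), at the end of the Background, is "to examine the temporal relationship between fear of falling, falls and function in the above population". The Background motivates it with an open question of direction: "whether a fall causes fear of falling, whether fear of falling precipitates a fall, or whether a third factor causes both". It asks for longitudinal data, with particular interest in what happens shortly after a fall.

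Under Fear of Falling Sub-Study, Procedures, assessments take place at baseline, "at four monthly intervals, and following any fall throughout the 12 month study period". The outcomes section makes fear of falling (FES-S), gait, balance and activity all primary. The sample size is 80.

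The sub-study's Statistical methods section has two sentences. The first uses descriptive statistics and MANOVA "to determine changes in fear of falling and physical function between control and intervention groups, and faller and non-faller groups over time". The second reads: "Time series analyses and individual case analysis will be used to identify links between fall events and changes in fear of falling".

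The sub-study does not define a faller. The main trial's Statistical methods section uses fallers and non-fallers as a summary of falls over follow-up, which makes a 12-month label the natural reading here too.

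**The concern.** Aim (ii) is about order in time. A fixed faller/non-faller factor is an outcome that becomes known during or at the end of the year. If it labels a person at baseline, month 4 and month 8, someone who first falls in month 11 is a faller throughout. Scores that precede the fall and scores that follow it are then averaged in one group.

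Post-fall assessments occur only in fallers, at irregular times and in varying number. A MANOVA over common time points cannot take them in, although they bear most directly on the short-term effect of a fall.

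At stake is the interpretation of the sub-study. A faller/non-faller difference could be reported as a consequence of falling when part of it was present beforehand. The trial's primary result is not affected.

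**Working it through.** **No figure to reproduce.** The article gives no power, effect size or other number for this comparison. The check sets the analyses against the aim and then sizes the mixing.

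**Analyses named, by question**

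| Question within aim (ii) | Grouped MANOVA | Event-timed analysis named |
|---|---|---|
| Fear after a fall | yes | yes (time series, case analysis) |
| Function, gait, balance, activity after a fall | yes | none |
| Falls after earlier fear | only through a baseline gap | none |

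**Share of eventual fallers still pre-fall at month t.** Inputs: 12-month faller proportion p = 75% (usual care) and 50% (intervention), from the main trial's Sample Size section; visits at months 0, 4, 8 and 12, from Procedures. Assumptions: a faller is anyone with at least one fall in 12 months counted from baseline, and the hazard is constant.

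F(t) = 1 − (1 − p)^(t/12); share still pre-fall = 1 − F(t)/p.

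- p = 0.75, month 4: F = 1 − 0.25^(1/3) = 0.370; share = 1 − 0.370/0.75 = 0.507.
- p = 0.75, month 8: F = 1 − 0.25^(2/3) = 0.603; share = 0.196.
- p = 0.50, month 4: F = 1 − 0.50^(1/3) = 0.206; share = 0.587.
- p = 0.50, month 8: F = 1 − 0.50^(2/3) = 0.370; share = 0.260.
- p = 0.625 (mean of the two): 0.554 and 0.232.
- Any p, baseline: F(0) = 0; share = 100%.

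**Early clustering.** The Background cites up to 73% falling in the first six months after discharge. Combine that upper figure with 75% at 12 months, and hold the hazard constant within each half-year:

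- Month 4: F = 1 − 0.27^(4/6) = 0.582; share = 1 − 0.582/0.75 = 0.224.
- Month 8: F = 1 − 0.27 × (0.25/0.27)^(2/6) = 0.737; share = 1 − 0.737/0.75 = 0.018.

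**What the grouped comparison can still show.** A simulation used assumed effects: standardised fear scores correlated 0.6 between visits; where fear drives falls, a log hazard ratio of 0.4 per SD; where falls drive fear, a lasting 0.3 SD rise for each interval with a fall; about 60% to 63% fallers. The faller minus non-faller gap in fear, in SD, was:

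| Scenario | Baseline | Month 4 | Month 8 | Month 12 |
|---|---|---|---|---|
| Fear drives falls only | 0.43 | 0.42 | 0.43 | 0.35 |
| Falls drive fear only | 0.00 | 0.13 | 0.27 | 0.40 |
| Both | 0.43 | 0.57 | 0.70 | 0.77 |

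The pattern of gaps therefore carries some information on direction. It does not tie a change to the time of the fall: at month 12 the first two scenarios give 0.35 and 0.40, almost the same gap.

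**The case against.** The strongest reply is that the plan does not rest on the MANOVA for event timing. The second sentence of the section gives the link between falls and changes in fear to time series and individual case analyses, and the post-fall assessments supply data for them. Counting only the four scheduled points understates those data, because fallers have extra ones. This stands for fear of falling. It does not reach function, gait, balance or activity, and it names no analysis with falls as the outcome.

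A reader might infer that the sub-study cannot answer its temporal aim at all. The documents do not support that. A baseline gap between later fallers and non-fallers is prospective evidence on whether fear comes first, and the aim is to examine a temporal relationship, not to prove a cause.

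Three further points stand:

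- The 12-month definition of a faller is inferred. A condensed article may leave it to the full protocol.
- How MANOVA would treat missed visits is ordinary analysis-plan detail and forms no part of this point.
- The constant-hazard shares are not robust. Early clustering takes them well below 51% and 20%. None of the shares measures bias in an estimate.

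**Conclusion.** The point holds in a limited form. The faller/non-faller MANOVA is a stated method that fits aim (ii) poorly: on the natural reading it groups earlier scores by later falls, pools pre-fall with post-fall measurements and leaves out the post-fall assessments. Event timing is addressed for fear of falling only, and no analysis has earlier fear predicting later falls.

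All eventual fallers are pre-fall at baseline. At month 4 the share is 51% to 59% under a constant hazard, or about 22% with strong early clustering; at month 8 it is 20% to 26%, or about 2%. These figures rest on the 12-month definition, on counting from baseline and on the assumed hazard shapes. The mismatch itself depends on the faller definition but not on the hazard. It is worth correcting, but it concerns a sub-study aim and not the main trial.

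**What to change.** Label the faller/non-faller MANOVA descriptive and state over what period a faller is defined. For aim (ii), name two analyses on the data already planned:

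1. A linear mixed model for FES-S, gait, balance and activity on all scheduled and post-fall assessments, with a participant random effect, arm, time and time-updated fall status (for example any falls or cumulative falls to date, or time since the most recent fall). Do not combine falls since the last assessment with an indicator for unscheduled visits: every fall triggers an assessment, so the two terms are nearly collinear. Instead, add a sensitivity analysis restricted to scheduled visits.
2. An interval count or recurrent-event model for falls in the next interval, with the preceding FES-S as a lagged predictor, adjusted for arm and prior falls.

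The time series and case analyses can stay as exploratory description. Both models show order in time; neither by itself rules out a third factor. The cost is slightly more complex analysis and reporting, with no new data.

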### Obstacle Crossing Sub-Study

Participants recruited in the primary study from both intervention and control groups through Melbourne sites will be approached to participate in an additional measurement session at twelve months following enrolment in the study. It is anticipated that 30 subjects will be recruited for this sub-study.

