#### Procedure

During testing, subjects will wear shorts and singlet to allow marker application. They will also wear well-fitting shoes and any prescribed eyewear usually worn during ambulation. Reflective markers will be placed on the lower limbs and trunk using double sided adhesive tape. Motion of the reflective markers will be recorded by the VICON^® ^motion analysis system. Data on centre of pressure (COP) will be collected using the AMTI forceplates. Subjects will perform three or four walks at a comfortable speed. They will then be asked to perform eight trials where they walk and step over a 4 cm high obstacle, placed in the middle of the walkway. Subjects will be cautioned to perform the tasks within their limits of safety and stop if they feel at risk at any time.

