#### Statistical Analysis

Data will be compared with normative data using multivariate analysis of variance. Adjustment will be made for any covariates which may impact on obstacle crossing, such as leg length. Performance on the primary gait measures will be compared between participants in the experimental and control groups of the randomised controlled trial, using multivariate analysis of variance, with adjustment for covariates identified as differing between the two groups at this measurement occasion.

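### The obstacle-crossing sub-study compares self-selected 12-month volunteers as the trial's randomised arms, and its planned adjustment does not restore that comparison

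*Protocol article*

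**What the plan says.** The Obstacle Crossing Sub-Study draws on "Participants recruited in the primary study from both intervention and control groups through Melbourne sites", who "will be approached to participate in an additional measurement session at twelve months following enrolment in the study". On size it says only that "It is anticipated that 30 subjects will be recruited for this sub-study". It gives no rule for choosing the 30.

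Under Procedure, the session opens with a few unobstructed walks at the subject's own pace. The obstacle task comes next: "They will then be asked to perform eight trials where they walk and step over a 4 cm high obstacle". The same section adds: "Subjects will be cautioned to perform the tasks within their limits of safety and stop if they feel at risk at any time".

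The sub-study's Statistical Analysis section plans two comparisons. One is against normative data. The other is between arms: "Performance on the primary gait measures will be compared between participants in the experimental and control groups of the randomised controlled trial". The arm comparison uses multivariate analysis of variance, adjusted for covariates found to differ between the groups at that session.

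The Background gives the reason for looking at gait: "Examination of stability during walking will provide insight into the mechanisms by which the intervention may have an effect on reducing falls". The Randomisation section places allocation directly after the baseline assessment. The Intervention section describes a home exercise programme with strength, balance and walking components, reviewed over the 12 months.

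**The concern.** Randomisation protects a comparison of everyone allocated. It does not protect a comparison of a minority who agree to an extra session and complete a demanding task after a year of treatment. If the programme changes who is willing or able to do that task, the two groups tested differ in more than treatment.

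The planned adjustment does not repair this. Covariates are chosen because they differ at 12 months. Such a difference may be an effect of the intervention, an effect of selection, or chance. Adjusting for a treatment effect removes part of what the comparison is meant to show, and adjusting for a 12-month variable does not recreate the baseline balance that selection has disturbed.

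At stake is the interpretation of mechanism. The Background asks whether fewer falls would reflect better stability or more caution. A stability difference that selection has shrunk could be read as support for caution.

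**Working it through.** **The figure of 30.** The article gives no effect size, SD, significance level or power for it, so there is nothing to reproduce.

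**Room for selection.** The Fear of Falling Sub-Study, which also uses the Melbourne sites, states that "approximately half of the overall sample will be included in this sub-study, giving a sample size of 80". Half of the planned 214 is 107, and 107 × 0.75 = 80.25, so the 80 is consistent with half the sample after the planned 25% dropout. The share of Melbourne participants tested is therefore 30/80 = 37.5%, or 30/107 = 28%. Most would not be in the comparison.

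**Sequence.** Baseline assessment, then allocation, then 12 months of exercise intervention, then attendance at the session, then completion of the task. The last two steps follow treatment, whenever the invitation is made.

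**Illustration 1: a strict cutoff (assumed).** Let 12-month walking ability be normal with SD 1 in each arm and a true arm difference d = 0.30. People enter only above a cutoff c. The difference among entrants is

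d + φ(c − d)/[1 − Φ(c − d)] − φ(c)/[1 − Φ(c)].

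With 70% of controls entering, c = −0.524. The control mean is 0.3477/0.70 = 0.497. The intervention mean is 0.30 + 0.2840/0.7951 = 0.657. The difference is 0.160. In the same way:

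| Controls entering (assumed) | Difference among entrants (true 0.30 SD) |
|---|---|
| 90% | 0.226 |
| 80% | 0.188 |
| 70% | 0.160 |
| 50% | 0.119 |

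**Illustration 2: gradual selection (assumed).** Entry is logistic in ability, with overall entry set to 37.5%. The slope is the log odds of entry per SD of ability. For a true 0.30 SD, simulation gives:

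| Slope | Entry, control / intervention | Difference among entrants |
|---|---|---|
| 0.5 | 36% / 39% | 0.286 |
| 1 | 35% / 40% | 0.248 |
| 2 | 33% / 42% | 0.184 |

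Numerical integration gives 0.284, 0.248 and 0.182, so the simulation error is small. At slope 2, and assuming that baseline ability explains 70% of the variance at 12 months, entrants in the intervention arm have baseline ability about 0.10 SD lower than control entrants. That is the loss of randomised balance, and baseline measures can address part of it.

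The two illustrations together run from about 0.29 to 0.12 SD. A strict cutoff at 37.5% overall entry is more extreme still, at about 0.09 SD. With no dependence of entry on ability there is no attenuation.

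**Precision.** If the 30 split 15:15 (assumed), the standard error of a standardised difference is √(2/15) = 0.37 SD. The difference detectable with 80% power is (1.96 + 0.84) × 0.365 = 1.02 SD. The largest shift in the 0.29 to 0.12 range is 0.30 − 0.12 = 0.18 SD, about half a standard error.

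**The case against.** A reader might infer a stronger fault: that people are recruited only at 12 months, that entry is restricted to those able to cross an obstacle, that anyone who stops is missing from every measure, and that the effect is roughly halved. The article does not support this.

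- The words on twelve months may describe the session rather than the approach, so an earlier invitation is possible.
- No walking criterion is written. Dependence on ability is an inference from the task and from voluntary attendance.
- With eight trials planned, someone who stops early may still contribute completed ones. The handling of incomplete trials can properly be left to an analysis plan.
- The halving comes from a hard cutoff on the outcome variable itself, with assumed inputs. Gradual selection at slopes 0.5 and 1 takes away much less.

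It is also fair to say that the article calls the sub-study cross-sectional, that its stated aim concerns gait impairment in obstacle crossing, and that the Background promises insight into mechanism, not a decisive test. Noise in 30 people would exceed most of the biases illustrated.

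What still stands is that nothing in the article fixes the sample before allocation, that attendance and completion come after treatment on any reading, and that the arms are still compared as the trial's groups with adjustment for 12-month differences. A small sample limits precision but does not excuse a systematic error in interpretation.

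**Conclusion.** The concern holds as a minor point about the between-arm analysis of this sub-study. That analysis is not a randomised comparison, and adjusting for covariates found to differ at 12 months neither makes it one nor is harmless. The documents determine neither the size nor the direction of the bias. Attenuation follows only if better walkers enter more often, and the figures above rest on an assumed 0.30 SD effect and assumed selection. The comparison with normative data, the falls outcome and the main trial's analysis are not affected.

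**What to change.** 1. Seek sub-study consent from Melbourne participants at the baseline visit, before allocation, and invite consenters in a pre-set order within each arm.
2. Record, and report by arm, how many were approached, declined, were unable, and completed the task.
3. In the sub-study's Statistical Analysis section, replace adjustment for covariates that differ at 12 months with adjustment for a few named baseline measures already collected, for example Step Test or gait velocity. With about 30 people the list must be short.
4. Attendance at 12 months remains a post-randomisation event even with baseline consent. State in the same section that the arm comparison is exploratory and made among volunteers who completed the task, and that no causal conclusion about mechanism will be drawn from it.

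The cost is one consent item at a visit already planned and a simple entry and completion record. Some baseline consenters will not attend at 12 months, and the sub-study's stated conclusion becomes more modest.

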#### Apparatus

A VICON^® ^motion analysis system and AMTI forceplates will be used to collect kinematic and kinetic data. Data will be processed and analysed using BodyBuilder^® ^software, which is designed for use with the VICON^® ^system.

#### Procedure

During testing, subjects will wear shorts and singlet to allow marker application. They will also wear well-fitting shoes and any prescribed eyewear usually worn during ambulation. Reflective markers will be placed on the lower limbs and trunk using double sided adhesive tape. Motion of the reflective markers will be recorded by the VICON^® ^motion analysis system. Data on centre of pressure (COP) will be collected using the AMTI forceplates. Subjects will perform three or four walks at a comfortable speed. They will then be asked to perform eight trials where they walk and step over a 4 cm high obstacle, placed in the middle of the walkway. Subjects will be cautioned to perform the tasks within their limits of safety and stop if they feel at risk at any time.

